### **Study termination**

The study will be discontinued in the event of any of the following:

- New scientific information is published to indicate that volunteers in the study are being exposed to undue risks as a result of administration of the IMPs by any route of administration, or as a result of the follow-up schedule.
- Serious concerns about the safety of the IMPs arise as a result of one or more vaccine related SAE occurring in the subjects enrolled in this or any other ongoing study of the IMPs.
- For any other reason at the discretion of the Principal Investigator.

### **Definition of the Start and End of the Trial**

The start of the trial is defined as the date of the first vaccination of the first volunteer. The end of the trial is the date of the last visit of the last volunteer.

## **9. ASSESSMENT OF SCIENTIFIC OBJECTIVES**

### **Lead-in Safety Evaluation**

Assessment of the safety and reactogenicity of ChAd63 ME-TRAP / MVA ME-TRAP prime-boost vaccination will be undertaken by summary listing of all solicited and unsolicited local and systemic adverse events (including results of clinical laboratory investigations where deemed adverse events), considered possibly, probably, or definitely related to vaccination; and line listing of all SAEs.

### **Phase 2b trial**

A full detailed statistical analysis plan will be developed prior to any unblinding of the data. The first data analysis will be performed after the last enrolled participant has reached 6 months after last vaccination. Analyses for the subsequent follow-ups will be carried out when all participants have reached at least 12 months and 24 months after the last vaccination, except extension of the efficacy analyses to 24 months will be dependent on the outcome of the efficacy analyses of the 12 month data. Results of these analyses will be disseminated accordingly.

Investigators performing the statistical analyses will be unblinded to Group B vs C allocation once all data to 6 months following enrolment of all volunteers is collected and data locked. Investigators not performing the analyses, for example those undertaking field work and interpreting adverse events and malaria endpoints, will remain blinded until the end of the study.

The According-to-Protocol population for the statistical analyses are those participants who are eligible to participate, and received both allocated vaccines within the specified time window periods without any contraindications to vaccine administration.

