\* Depending on the outcome of the efficacy analysis of the 12 month data, this may be extended to 24 months following completion of vaccination

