| Blood sampling                                                                                          | X           | X ++ , X + |            |       | X      | X ++       |             | X     |     |                     | X    |                          | X    |                                                       | X    |

\*\* Each study visit will occur the indicated number of days from Day 0, within the window period for that visit

S: Screening Visit;      X: procedure takes place,      (X): procedure takes place as required at the discretion of the investigators;  
D : Day.

\* if efficacy analysis is extended to include data to 24 months following completion of vaccinations

+: nested cohort of Group B and C volunteers only

++: Group A volunteers only

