### Secondary Objectives

#### *Duration of Protective efficacy against clinical malaria*

To assess the protective efficacy against clinical malaria of ChAd63 ME-TRAP / MVA ME-TRAP prime-boost immunisation, in 5-17 month old infants and children living in a malaria-endemic area, for 12 and 24\* months after the last vaccination.

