## Study site

The study will take place at the Banfora trial site, which is located about 400 km from Ouagadougou, the capital city of Burkina Faso. The URC-B, the research unit is situated within the complex of the Regional hospital. The trial participants will be drawn from Banfora Health demographic system that covers a total population of 30,000 inhabitants. From recent surveys, the bed net coverage was 80%. There is no implementation of Indoor Residual Spray or IPT in infants or children in the area. To date there is no evidence of the decline in malaria incidence that has been recently reported from other parts of sub-Saharan Africa. In Burkina Faso, malaria is endemic. Transmission occurs throughout the year, with a peak during the rainy season (June to October). *P. falciparum* is responsible for more than 90% of all clinical malaria cases. The major vectors are *Anopheles gambiae*, *An. arabiensis* and *An. funestus*. Children under five years and pregnant women are the populations at highest risk. During the five months when transmission reaches a peak, individuals in these age-brackets may suffer multiple malaria episodes, with an annual malaria death toll reaching 15,000 people. In the country's hospitals, malaria is reportedly responsible for 30.7% of all hospitalization with a mortality rate of 23%.

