## Sample size

For the Lead-in Safety Evaluation, a sample of size of 30 participants has been selected as the minimum number required to provide adequate safety data to enable an interim assessment of safety which could support progressing to the Phase 2b trial.

The primary endpoint of the Phase 2b trial is the time to first episode of malaria meeting the primary case definition of clinical malaria episode, over a period of 6 months. We will aim to time vaccinations so that this 6 month interval (study day 63 to 243) incorporates the malaria season, which runs from June to October.

From the results of a baseline site survey, it is anticipated that during the malaria season, the incidence of malaria meeting the primary case definition of clinical *P. falciparum* malaria episode will be 50% in 5-17 month old infants. Rabies vaccination should not provide any protection against malaria infection. Therefore, the incidence of episodes meeting the primary case definition of clinical *P. falciparum* malaria between Day 63 and Day 243 in Group C should be 50%.

An efficacy of vaccination of 30% is that considered suitable for the vaccine strategy to be included in a future multi-component high efficacy vaccine. With a total sample of 700 participants, the expected power to detect 30% vaccine efficacy, (i.e., a hazard ratio of 0.7, with the proportion of malaria in Group B by Day 243 equalling 38%) will be 88%. Due to the short duration of the study, we anticipate the rate of loss to follow-up or drop out will be minimal. However, even with 20% drop-out or loss to follow-up, the sample size still gives 80% power to detect 30% vaccine efficacy.

| Proportion who develop clinical P. falciparum malaria in Group C | Proportion who develop clinical P. falciparum malaria in Group B | Hazard ratio | Power |
|-------------------------------------------------------------------------|-------------------------------------------------------------------------|--------------|-------|
| 50%                                                                     | 38%                                                                     | 0.7          | 88%   |
| 40%                                                                     | 30%                                                                     | 0.7          | 79%   |

Table 2: Power to assess 30% efficacy of vaccination in the Phase 2b trial

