### ***Study duration and timeline***

Proposed timeline for the study:

| Date                   | Activity                                              |
|-------------------------------|--------------------------------------------------------------|
| October 2012                  | Commencement of Recruitment                                  |
| December 2012                 | First vaccination of Group A participants                    |
| January- February 2013        | Second vaccination of Group A participants                   |
| March-April 2013              | First vaccination of Group B and C participants              |
| May 2013                      | Second vaccination of Group B and Group C participants       |
| May/June 2013 – December 2013 | Collection of endpoints for the primary analysis of efficacy |
| To May 2015                   | Efficacy*, safety, and immunogenicity follow-up              |

Depending on whether significant efficacy is seen, and the potential of the vaccines for licensure, we may consider extending the follow up further for pharmacovigilance purposes. In such a case, informed consent will be obtained from study participants.

\* Depending on the outcome of the efficacy analysis of the 12 month data (to June 2014), this may be extended to 24 months following completion of vaccination.

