**Day 783**

Medical history, temperature monitoring +/- physical examination will be performed.

Blood sampling will be performed as detailed below (Laboratory Evaluations). The CRF will be updated, including the records of SAEs and concomitant medications.

A blood smear will be obtained for malaria diagnosis.

Information regarding the reported ethnolinguistic or tribal identity of the participant and their mother and father will be collected as part of the Add On Study 1 in one of the visits before the end of the follow-up period.. This information will be used specifically to aid interpretation of the genetic analyses.

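### The 24-month efficacy analyses depend on the unblinded 12-month result, so protection in the second malaria season is either not analysed or reported after selection

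*Protocol*

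**What the plan says.** The condition stands in four places in the protocol: the Section 1 synopsis footnote, the footnote under Study duration and timeline in Section 5, the Phase 2b trial text in Section 9, and the footnote closing the secondary efficacy analyses in Section 9. The Section 9 text plans analyses at each follow-up, "except extension of the efficacy analyses to 24 months will be dependent on the outcome of the efficacy analyses of the 12 month data". The synopsis footnote reads "Depending on the outcome of the efficacy analysis of the 12 month data, this may be extended to 24 months following completion of vaccination". The timeline footnote dates the look: "Depending on the outcome of the efficacy analysis of the 12 month data (to June 2014". None of the four gives a threshold, a direction or a decision-maker. Under Section 9 the analysts are unblinded after the 6-month data lock, while field and endpoint staff stay blinded to the end of the study.

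Duration of protection is the first secondary objective, at 12 months and, starred as conditional, at 24 months. The sample size text says that the primary window should be one that "incorporates the malaria season, which runs from June to October". The timeline plans first vaccination of Groups B and C in March-April 2013 and second vaccination in May 2013.

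Follow-up lasts 26 months from Day 0 for everyone. Section 8 has monthly home visits to Day 753, with febrile children referred for a film, and a clinic visit with blood sampling at Day 783. On the film at Day 783 the documents disagree. The visit text says "A blood smear will be obtained for malaria diagnosis" without condition, whereas Tables 1 and 3 take it only "if efficacy analysis is extended to include data to 24 months following completion of vaccinations".

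**The concern.** Where malaria is seasonal, durability is mainly a question about the next season. If the 12-month window contains only one season, the 12-month look cannot answer it, and the 24-month analysis is the only planned one that can.

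Letting a known treatment result decide whether that analysis is done has two consequences. First, some trials would never report second-season efficacy. Second, where it is reported, the estimate is conditioned on an earlier estimate built from many of the same first episodes. If the condition favours good 12-month results, the reported 24-month efficacy is too high on average.

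**Working it through.** **1. The plan's own figure.** Inputs from Sample size (Section 5): 700 children, 1:1, 50% v 38% with malaria by Day 243, hazard ratio 0.7. A two-sided alpha of 0.05 is assumed from the 95% interval.
- Events = 350 × (0.50 + 0.38) = 308.
- Power = Φ(½·√308·|ln 0.7| − 1.96) = Φ(3.13 − 1.96) = Φ(1.17) = 87.9%, against 88% stated.
- The other two stated powers also reproduce: 79.7% (79% stated, 40% v 30%) and 79.9% (80% stated, with 20% drop-out).

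The primary analysis is not in dispute.

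**2. Which seasons each window covers.** Season 1 June to 31 October, 153 days. Day 63 is 7 days after the second vaccination.

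| Planned dates | Day 63 | Day 423 | 2013 season days, Day 63-243 | 2013 season days, Day 63-423 | 2014 season days, Day 63-423 |
|---|---|---|---|---|---|
| Second dose 1 May 2013 | 8 May 2013 | 3 May 2014 | 153 | 153 | 0 |
| Second dose 31 May 2013 | 7 Jun 2013 | 2 Jun 2014 | 147 | 147 | 2 |
| Day 0 on 30 Apr 2013 (latest) | 2 Jul 2013 | 27 Jun 2014 | 122 | 122 | 27 |

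The 6-month window already holds the peak-season days of 2013, so the 12-month window adds almost no peak exposure. Ending at Day 738 or at Day 783 adds all 153 days of the 2014 season. The 12-month data close around June 2014, just as that season starts, so a decision based on them falls during or after it. Endpoints for the season must therefore be collected before the decision or be lost.

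**3. How much of the 12-month result is the 6-month result.** The documents do not give the low-season risk, so a range is shown for the control group.
- Assume 10%: later first episodes = 0.50 × 0.10 = 0.05; share in the first six months = 0.50/0.55 = 91%.
- Assume that the pilot rate of 0.09 per child-month (Section 5, passive surveillance) is a year-round average for the same case definition, which the protocol does not say: 12 × 0.09 = 1.08 a year. The 50% risk uses −ln 0.5 = 0.69, leaving 0.39, a risk of 1 − e^(−0.39) = 32%. Later first episodes = 0.50 × 0.32 = 0.16; share = 0.50/0.66 = 76%.

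**4. Size of the selection.** The gate is assumed to be a significant benefit at 12 months. Each scenario uses 4,000 simulated trials with 350 per arm. The main set uses a Cox model, 50% control risk per season and no off-season events. The 15% row comes from a second set with 10% low-season risk and a stratified rate ratio. Efficacy is the median in the main set and the mean in the second.

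| True efficacy, season 1 / season 2 | 24-month analysis run | 24-month efficacy, all trials | 24-month efficacy, gated trials |
|---|---|---|---|
| 30% / 30% | 89% | 30% | 31% |
| 30% / 0% | 88% | 20% | 21% |
| 20% / 20% | 51% | 20% | 24% |
| 20% / 0% | 51% | 13% | 18% |
| 15% / 15% | 33% | 15% | 21% |
| 10% / 10% | 15% | 10% | 19% |

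In the second set, a true efficacy of 30% gives 31% v 30%, with 9% of trials not reporting. The main set gives 11-12% not reporting.

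**The case against.** The strongest reply is that this is a declared, staged design. The 24-month efficacy element is starred in the objectives, the 12-month analysis is unconditional, and variation of efficacy over time is to be examined with Schoenfeld residuals and time-dependent covariates. That stands. A reader might infer that the whole duration objective goes unanswered; the documents do not support this, since only second-season efficacy is at stake. Transmission is also year-round according to the Study site text, so the 12-month data carry some low-season information.

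A second reply is that the criterion may sit in the statistical analysis plan, which Section 9 says is written before unblinding. This also stands: a missing threshold is not itself the point. But such a plan could only add a threshold to the dependence; it could not remove it without contradicting the protocol.

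Third, a reader might infer that 24-month efficacy is reported only if the 12-month result is good. The protocol says only that the extension depends on the outcome, so every figure in step 4 rests on an assumed direction and rule.

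Fourth, a reader might infer that later harm would never be seen. That goes too far. Serious adverse events are collected to the end of the study and compared between groups, and they include hospitalisation. On a plain reading, hospitalised malaria outside an efficacy evaluation would still count. What would lack a planned comparison is uncomplicated second-season malaria, because non-serious events are recorded only to 30 days after vaccination.

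Finally, removing the condition is not free. The primary case definition relies on continuous clinic-based detection, slide reading and blinded adjudication, and the timeline stars efficacy follow-up itself.

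**Conclusion.** The point holds for second-season protection. As written, the plan makes the only analysis covering the 2014 season depend on an unblinded result drawn essentially from the 2013 season. The season count follows from the protocol's own dates and needs no modelling assumption.

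The size does need assumptions. With a significance gate at 12 months, the inflation at the 30% efficacy used for the sample size is about 1 point, and the main loss is the 9-12% of trials that never report season 2. At a true efficacy of 10-20% the inflation is about 4 to 9 points, and 49% to 85% of trials do not report. A different gate would change these figures. The share of 12-month first episodes falling in the first six months is likewise an assumption, plausibly 76% to 91%. The primary analysis and its power are unaffected, so this is a change that should be made rather than a fault in the main result.

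**What to change.** In the protocol:
- Delete the condition in the synopsis footnote, Study duration and timeline, the Phase 2b trial text of Section 9 and the footnote to the secondary efficacy analyses. Remove the matching stars in the synopsis objectives, the Section 4 secondary and exploratory objectives, the Section 9 secondary efficacy analyses and the Exploratory Analysis.
- State that the 24-month efficacy analyses are done and reported whatever the 12-month result.
- Reconcile the Day 783 film (unconditional in the visit text, conditional in Tables 1 and 3) so that it is taken from every child.
- Reconcile the 24-month time point. The Section 9 secondary analyses use Day 738 (738 − 63 = 675 days), while the visit schedule uses Day 783 (720 days).
- Report efficacy from Day 423 onward separately, as a supportive analysis.

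Cost: passive case detection, slide reading and endpoint adjudication continue through the second season, one more analysis is run, and a null 24-month result must be reported. No extra visits or children are needed. Stating the criterion before unblinding would be a lesser remedy: it removes the arbitrariness but not the selection.

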| Primary Evaluation Endpoint: Phase 2b Trial            | Time to first episode of malaria meeting the primary case definition of clinical malaria episode ± over a period of 6 months of follow-up after the last vaccination (i.e., from study day 63 to study day 243).                                                                                                                                                                                                                                                                                                                                                                                                                                                                                                                                                                                                                                                                                                                                                                                                                                                                                                                                                                                                                                                                                                                                                                                                                                        |

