## **Allocation of participants to Study Group and order of enrolment of Study Groups**

Participants are considered enrolled into the study when they have received the first study vaccination.

The study will commence with the Phase 1 lead-in Safety Evaluation. Thirty eligible participants will be identified as above, and allocated to Group A. The participants will be the following ages at enrolment:

- 5 to 8 months: 10 participants
- 9 to 12 months: 10 participants
- 13 to 17 months: 10 participants

For the Phase 2 Trial, 700 eligible participants will be identified as above, and randomised to Group B or C by an independent statistician, who is not one of the investigators. The randomisation will be stratified according to the following age categories, with varying block sizes:

- Participants aged 5-8 months at enrolment
- Participants aged 9-12 months at enrolment
- Participants aged 13-17 months at enrolment

A randomisation list will be generated and sequentially numbered opaque sealed envelopes will be made for the investigators to ensure treatment concealment. The investigators will not be aware of the randomisation result in the envelopes. The randomisation list, which will be password protected, will be kept in confidence until the final primary analysis is being conducted. As described in Section 7, all investigators will be blinded to allocation of participants in the Phase 2b trial to Group B vs Group C, except the staff responsible for the storage and preparation of the study vaccines.

The interim safety data to Day 21 of trial participation of Group A participants will be presented to the DSMB. DSMB review and approval will be required to administer the first vaccination to Group B and C participants.

The interim safety data to Day 63 of trial participation of Group A participants will be presented to the DSMB. DSMB review and approval will be required to administer the second vaccination to Group B and C participants.

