### **Day 0 (Vaccination)**

This visit will occur not more than 30 days following the screening visit. If more than 30 days have elapsed since screening, then a repeat Screening Visit will be conducted. Medical

history, temperature monitoring +/- physical examination will be performed. Blood sampling will be performed as detailed below (Laboratory Evaluations).

Ongoing eligibility for participation will be confirmed according to the inclusion and exclusion criteria, prior to blood sampling and vaccination. Blood sampling will be performed as detailed below (Laboratory Evaluations).

Infants are considered enrolled into the study when they receive the first study vaccination. The vaccine will be administered as detailed in Section 7 and according to local SOPs.

Following vaccination, the vaccination site will be covered with a dressing which will be removed after 30 minutes. The volunteer will be monitored for one hour (or longer if necessary) after vaccination.

The CRF will be updated.

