### **Ascertainment of malaria Endpoints**

Collection of malaria endpoints for analysis of efficacy will begin at Day 63, which is 7 days following of completion of the vaccination regimen.

Clinically qualified investigators will adjudicate the presence of the endpoints of clinical *P. falciparum* malaria, severe *P. falciparum* malaria, and asymptomatic *P. falciparum* carriage, before they are unblinded to Group B vs C allocation.

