### ***Primary analysis***

The primary analysis of efficacy will be comparison between Group B and C of the time to first episode of malaria meeting the primary case definition of clinical malaria episode over a period of 6 months of follow up after the last vaccination (ie, from Day 63 to 243). This will be done using survival analysis (e.g. Cox proportional hazard model), adjusting for any stratification factors (age, bednet use). Results will be presented as adjusted hazard ratio with appropriate 95% confidence intervals. Vaccine efficacy will be calculated as 1-HR. Kaplan-Meier methods will be used to visualize the time to first malaria event. The primary analysis will be based on the per-protocol population. An unadjusted analysis will also be carried out on the basis of intention-to-treat.

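### The rule for analyst unblinding and data lock counts from enrolment (Day 0), so for the last child enrolled it falls 60 to 63 days before the primary window closes on Day 243

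*Protocol*

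**What the plan says.** Section 9 of the protocol, under Phase 2b trial, gives two timings in consecutive paragraphs.

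- First analysis: "The first data analysis will be performed after the last enrolled participant has reached 6 months after last vaccination".
- Unblinding of the investigators who perform the analyses: "once all data to 6 months following enrolment of all volunteers is collected and data locked".

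The same paragraph limits who is unblinded. Investigators who do not perform the analyses, such as "those undertaking field work and interpreting adverse events and malaria endpoints, will remain blinded until the end of the study".

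Enrolment is a defined term. Section 8, on allocation to study groups, says: "Participants are considered enrolled into the study when they have received the first study vaccination". The Day 0 visit description repeats it: "Infants are considered enrolled into the study when they receive the first study vaccination".

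The primary endpoint is counted from the end of vaccination. The synopsis gives the window as "from study day 63 to study day 243", and the Primary analysis subsection has "over a period of 6 months of follow up after the last vaccination (ie, from Day 63 to 243"). Section 8, on ascertainment of malaria endpoints, adds: "Collection of malaria endpoints for analysis of efficacy will begin at Day 63, which is 7 days following of completion of the vaccination regimen".

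Two other provisions bear on timing. The timeline in section 5 puts first vaccinations of Groups B and C in March to April 2013 and collection of primary endpoints up to December 2013. Section 8 keeps the password-protected randomisation list confidential until the final primary analysis is under way.

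**The concern.** Two clocks govern the same event. One starts at the first vaccination and the other at the second, eight weeks later. The sentence that controls analyst unblinding and the lock uses the earlier clock, while the endpoint and the first analysis use the later one.

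A team that followed the sentence to the letter would lock the data and release allocation to its analysts while some children were still inside the primary window. Two things would suffer:

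- **Analyst blinding.** Decisions on data handling for the remaining follow-up would be made by people who know the allocation.
- **Completeness of the lock.** For late enrollees the locked data would lack the last part of the primary window. They would also lack the Day 213 record of bednet use, which is an adjustment factor in the primary model, and the Day 243 smear, which supplies the 6-month result for asymptomatic infection.

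**Working it through.** **Inputs**

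- Trigger: 6 months after enrolment of all volunteers (section 9, Phase 2b trial).
- Enrolment: first vaccination, Day 0 (section 8).
- Second vaccination: Day 56. Primary window: Day 63 to Day 243 (synopsis; section 9, Primary analysis).
- Length of 6 months: 180 days on the protocol's 30-day visit grid, or about 183 calendar days. Both are carried through.
- Calendar: first vaccinations March to April 2013, primary endpoints to December 2013 (section 5).

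**1. The plan's own window.** 56 + 7 = 63, and 63 + 6 × 30 = 243. This reproduces the stated close. Window length: 243 − 63 = 180 days.

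**2. Where the trigger falls for the last child enrolled.** 0 + 180 = Day 180, or 0 + 183 = Day 183.

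**3. Gap to the close for that child.** 243 − 180 = 63 days, or 243 − 183 = 60 days. As a share of the window: 63/180 = 35%, or 60/180 = 33%.

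**4. Gap for other children.** A child enrolled d days before the last one has a gap of max(0, 63 − d) or max(0, 60 − d) days.

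| d (days before last enrollee) | Gap, 30-day months | Gap, calendar months |
|---|---|---|
| 0 | 63 | 60 |
| 30 | 33 | 30 |
| 60 | 3 | 0 |

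**5. Check against the calendar.** Assume that first vaccinations fill the planned slot, from 1 March to 30 April 2013.

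- A child enrolled on 30 April reaches Day 183 on 30 October and Day 243 on 29 December.
- A child enrolled on 1 March reaches Day 243 on 30 October.

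Collection of endpoints to December 2013 therefore fits the Day 243 clock and does not fit the trigger.

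**6. Check against the first-analysis sentence.** Six months after a Day 56 vaccination is 56 + 180 = Day 236, or 56 + 183 = Day 239. The two adjacent paragraphs are thus 56 days apart whichever month length is used. The protocol equates its 6 months after last vaccination with the Day 63 to 243 window. Counted strictly from Day 56 it falls 4 to 7 days short of Day 243, so a corrected sentence should name the day.

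**7. Check against the list rule.** The primary analysis needs follow-up to Day 243. A list held in confidence until that analysis is being done cannot also be released to analysts at about Day 183 of the last child.

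**The case against.** The strongest reply is that the phrase is a slip for last vaccination and would mislead nobody. The preceding paragraph, the synopsis, the primary analysis, the timeline and the confidentiality rule for the list all point to the later date. The statistical analysis plan must also be written before any unblinding. This makes actual early unblinding less likely, and it stands as a reason to see the defect as one mis-anchored sentence. It does not remove the defect: the sentence is the operative rule for analyst unblinding, and enrolment is defined twice, so its literal meaning is not in doubt.

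A reader might infer three stronger things that the documents do not support.

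- **That cases would be detected or adjudicated by unblinded staff.** Section 9 keeps field staff and those who interpret endpoints blinded to the end of the study, and section 8 requires adjudication before the adjudicators are unblinded. Only the analysing investigators are affected.
- **That the trial loses events and its stated 88% power falls.** An early lock does not authorise a primary analysis on shortened follow-up. The endpoint definition and the first-analysis sentence still require data to Day 243. Any figure for lost power would also need an assumed event rate over time. A constant hazard fits poorly with a peak season of June to October, because under the planned calendar the last child's missing days fall mainly in November and December.
- **That every child loses about 60 days.** The full gap belongs to the last child enrolled and shrinks day for day with earlier enrolment.

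**Conclusion.** The point holds as an internal contradiction in an operative rule on blinding and lock. As written, the trigger falls at about Day 180 to 183 of the last child enrolled, 60 to 63 days (33% to 35% of the window) before that child's primary follow-up ends. The gap is smaller for children enrolled earlier, down to 0 to 3 days for one enrolled 60 days before the last.

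The range depends only on whether a month is 30 days or a calendar month. The calendar dates assume accrual across the whole of March and April 2013.

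What is at risk is the analysts' blinding and the completeness of the locked data for late enrollees. Case ascertainment is not at risk, and no loss of power is claimed.

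**What to change.** Reword the one sentence in section 9 (Phase 2b trial). Investigators performing the analyses are unblinded only after three conditions are met:

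1. Every Group B and C participant has completed the primary window through Day 243 (6 months after the last vaccination), or has left follow-up before then.
2. All endpoints in that window have been adjudicated.
3. The database has been locked.

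Name Day 243 in the sentence, and use the same anchor in the first-analysis sentence so that the two cannot diverge.

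The cost is a wording change in the protocol. It adds no visits, procedures or participants. It does not delay the primary result, because that analysis already needs follow-up to Day 243.
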